## Abstract

**Background:**

Patients with acute brain injury often require invasive mechanical ventilation, increasing the risk of developing complications such as respiratory secretions retention. Rapid chest compression is a manual chest physiotherapy technique that aims to improve clearance of secretions in these patients. However, the rapid chest compression technique has been suggested to be associated with increased intracranial pressure in patients with acute brain injury. The aim of this work is to elucidate the effects of the technique on intracranial pressure in mechanically ventilated patients with acute brain injury. Furthermore, the effects of the technique in different volumes and flows recorded by the ventilator and the relationship between the pressure applied in the intervention group and the different variables will also be studied.

**Methods:**

Randomized clinical trial, double-blinded. Patients with acute brain injury on invasive mechanical ventilation > 48 h will be included and randomized in two groups. In the control group, a technique of passive hallux mobilization will be applied, and in the intervention group, it will be performed using the rapid chest compression technique. Intracranial pressure (main variable) will be collected with an intracranial pressure monitoring system placed at the lateral ventricles (Integra Camino).

**Discussion:**

The safety of chest physiotherapy techniques in patients at risk of intracranial hyperpressure is still uncertain. The aim of this study is to identify if the rapid manual chest compression technique is safe in ventilated patients with acute brain injury.

**Trial registration:**

NCT03609866. Registered on 08/01/2018.

## Administrative information

Note: the numbers in curly brackets in this protocol refer to SPIRIT checklist item numbers. The order of the items has been modified to group similar items (see http://www.equator-network.org/reporting-guidelines/spirit-2013-statement-defining-standard-protocol-items-for-clinical-trials/).

## Introduction

### Background and rationale {6a}

Critically ill patients on invasive mechanical ventilation (IMV) usually develop mucus retention, increasing the risk for associated morbidity [1–5]. Endotracheal intubation and inflation of the endotracheal tube cuff are associated with a drastic decrease of mucocilliar transportation (aprox. 10x) and imped an effective cough. Additionally, the semi-sitting position at 30°, which is currently recommended by international guidelines to prevent ventilator-associated pneumonia, may further hinder mucus clearance because of the gravity force in the greater caliber airways. Also, the use of sedative and relaxing drugs may inhibit cilia motility and respiratory muscles activation which increases mucus retention. Finally, associated comorbidities and recurrent respiratory infections also play an important role in the increased production of respiratory secretions [1–5].

Respiratory physiotherapy has been proposed as a potential strategy to prevent and/or reduce the retention of secretions in critical patients connected to invasive mechanical ventilation. The scientific evidence on the effectiveness of these techniques is not clearly conclusive and its safety has some related controversial. There are several publications that demonstrate the effectiveness of respiratory physiotherapy techniques in the mobilization of air volumes, expiratory flows, and respiratory secretions but still in an insufficient number so that clear evidence of effectiveness can be manifested in systematic review studies. Some of the respiratory physiotherapy techniques used in intensive care in ventilated patients try to modulate the ventilatory flows and improve the transport of mucus based on the double gas-liquid phase rationale. The use of these techniques is supported by laboratory evidence that mucus removal is enhanced when the expiratory flow is greater than the inspiratory flow. This is the case, for example, of the rapid chest compression technique, which aims to increase the expiratory flow and facilitate the transport of mucus to the exterior of the bronchial tree [1, 2].

In many studies, the effectiveness of the technique of rapid chest compression in the mobilization of secretions and peak expiratory flow is studied. Although in the work of Lima et al. (2008) [2] applied the thoracic compression technique, in one of its variants, to assess its effects in an animal model with atelectasis, using unilateral thoracic compression and concluding that the technique was not effective for the resolution of atelectasis with the mobilization of secretions. In a more recent work by Martí et al. (2013) [1], the technique of manual thoracic compression with different intensities was applied in pigs in IMV, and it was concluded that, with the rapid application of the technique, the secretions were mobilized outwards the bronchial tree. In this last study, controlled and randomized, the movement of respiratory secretions was studied by fluoroscopy in tracheostomized, sedated, and in IMV pigs [1, 2]. There are also studies that provide evidence of the technique of manual compression of the abdomen and chest in humans; Naue et al. (2011) [4] studied its effects associated with the increase of the support pressure to assess the amount of suctioned secretions without finding differences between groups. In 2014, the same authors published a randomized clinical trial in which they studied the increase in inspiratory pressure of 10 cmH20 associated with the technique of manual compression of the abdomen and chest with an increase in the amount of secretions suctioned, the volume of exhaled air, and improvement in the pulmonary dynamics. In the same 2014, Guimarães et al. [3] studied the effects of rapid thoracic compression on pulmonary mechanics, amount of secretions suctioned, and peak expiratory flow, finding significant differences in peak expiratory flow in the intervention group [3–5].

Although the effects of the different variants of the rapid chest compression technique in the mobilization of secretions, pulmonary dynamics, and expiratory flow continue to be studied, some authors devoted themselves to studying their effects in other systems and in certain pathologies in order to justify their use in specific clinical situations. This is the case of the effects of the manual rapid chest compression technique on intracranial pressure in patients with acute brain injuries. The first clinical trial on this matter was carried out by Thiesen et al. (2005) [6] where they studied the effects of some techniques of respiratory physiotherapy on intracranial pressure, among which manual thoracic compression with satisfactory results relative to the control of intracranial pressure was included; the conclusions were obtained without control group or randomization. Subsequently, Toledo et al. (2008) [7] studied the effect of vibro-compression on intracranial pressure in patients with cranio-encephalic trauma concluding that the respiratory physiotherapy maneuver did not increase intracranial pressure or cerebral perfusion pressure, this study was also performed without control group or randomization. Cerqueira-Neto et al. (2010) [8] and Cerqueira Neto et al. (2013) [9], also without a control, blind, or randomization group, studied the effects of the expiratory flow acceleration technique, one of the possible variants of the technique, in patients with traumatic brain injury, concluding that it did not significantly alter the intracranial pressure [6–9]. In a more recent study, Tomar et al. (2019) [10] in a randomized crossover trial comparing the manual chest percussion with the mechanical chest vibration concluded that the manual percussion was associated with ICP increase.

From the literature review, it can be verified that there is little scientific evidence on the safety of manual rapid chest compression in critically ill patients with acute brain injury in invasive mechanical ventilation [6–9, 11].

Patients with acute brain damage usually present respiratory complications associated with invasive mechanical ventilation and therefore could benefit from respiratory physiotherapy. However, the application of respiratory physiotherapy techniques in these patients could be associated with an increase in intracranial pressure [7–10, 12]. The maneuvers of respiratory physiotherapy can momentarily increase intrathoracic pressure, decreasing venous return and increasing intracranial pressure [6].

The intrathoracic pressure is directly related to the alveolar pressure and the manual rapid chest compression technique can increase momentarily the alveolar pressure. So, any technique that aims to increase the expiratory air flow must do it in a rapid way to avoid major intracranial pressure increases [6, 13–17].

According to the bibliography, the increase in intracranial pressure is a contraindication for the application of some techniques in patients with acute brain injury since it can cause a decrease in cerebral perfusion pressure if it is sustained over time or if it is not accompanied of a rise in the mean arterial pressure. The lowering of cerebral perfusion pressure leads to associated damage in the control mechanisms of blood supply in areas of penumbra, which will be responsible for part of the neuroplasticity in the recovery phases of acute brain injuries, with all its implications [10, 12, 18–20].

It is important to mention that different brain lesions may have different behaviors in terms of intracranial pressure and may present higher intervention risks [18].

Cerebral lesions with a hemorrhagic component imply a more aggressive control of the mean arterial pressure and intracranial pressure and may present extreme complications with punctual rises, as these pressure rises may cause an increase in hemorrhagic lesions due to fragility. The ischemic brain lesions may have an inverse behavior since decreases in mean arterial pressure or increases in intracranial pressure can lead to decreases in the cerebral perfusion pressure and make the penumbra areas suffer [18–21].

At present, there are no randomized clinical trials that have studied the effect of the manual rapid chest compression technique alone on intracranial pressure and that try to relate its behavior with the different kinds of acute brain injuries. Therefore, we believe that it is necessary to investigate the effects of the technique with the highest possible methodological rigor and quality [10–12].

We propose this study, trying to control as many variables as possible and studying the effects of a single technique, in order to provide methodologically sound conclusions.

### Objectives {7}

#### Main hypothesis

H0—The rapid chest compression technique does not produce a change in intracranial pressure in patients on invasive mechanical ventilation with severe acute brain injury.

H1—The rapid chest compression technique produces changes in intracranial pressure in patients on invasive mechanical ventilation with severe acute brain injury.

#### Objectives

##### Primary objective

To determine the effects of the rapid chest compression technique on intracranial pressure in patients on invasive mechanical ventilation with severe acute brain injury.

##### Secondary objectives

Establish a relationship between the type of brain injury and the behavior of intracranial pressure.

Establish a relationship between peak expiratory flow and behavior of intracranial pressure.

Establish a relationship between the pressure applied in the studied technique and the changes in the other dependent variables.

### Trial design {8}

Randomized controlled trial, double-blinded with a control group and intervention group.

## Methods: Participants, interventions, and outcomes

### Study setting {9}

The study protocol will be applied in the intensive care unit of the Hospital Álvaro Cunqueiro, a tertiary hospital in the southwest of Galicia; Spain.

### Eligibility criteria {10}

#### Inclusion criteria:

Intubated patients with mechanical ventilation in Volume Controlled, Pressure Controlled and Volume Controlled Pressure Regulated modes during the 48 h prior to the application of the techniqueSevere head injury with a GCS≤8 before sedation or after the surgical procedures, when needed.Hemodynamic stability (MAP> 65 mmHg)Respiratory stability (PEEP <10cmH_2_O and FiO_2_ < 60%)Intracranial Pressure Stability (0 <ICP < 20 mmHg)RASS sedation scale of − 5 pointsInformed consent obtained

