### Criteria for discontinuing or modifying allocated interventions {11b}

The interventions will stop if reached some of the safety values presented below or when the clinical team considers [11, 22, 23].

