**Table Tabb:** 

Safety limits	
40 bpm < **Heart rate** < 120 bpm	
60 mmHg < **Mean arterial pressure** < 110 mmHg	
− 10 mmHg < **Intracranial pressure** < 30 mmHg	
90% < **Oxygen saturation**	
50 mmHg < **Cerebral perfusion pressure**	

The rescue plan is the usual at our ICU to manage the pathological increases in the ICP: open drainage if exists, increase sedation, apply relaxation medicines and hypertonic solution, this in a step-by-step approach.

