### Recruitment {15}

The participants included in this study will be selected from the admitted patients with severe acute brain injury, ICP monitoring, and IMV in the ICU of the Hospital Álvaro Cunqueiro, Galicia, Spain. The number of patients that we had at our ICU with severe acute brain injury in 2019 was about 80. The selected patients must meet the following inclusion criteria: patients intubated with mechanical ventilation in controlled volume mode, controlled pressure and controlled volume controlled by pressure during the 48 h prior to the application of the technique; hemodynamic stability (MAP> 65 mmHg); respiratory stability (PEEP <10cmH_2_O and FiO_2_ < 60%); stability of intracranial pressure (0 <ICP < 20 mmHg); RASS sedation scale of 5 points; and informed consent obtained (Annex 1). Patients meeting any of the exclusion criteria will not be enrolled: thoracic fractures: costal, sternal, clavicular, scapular or unstable vertebral; abdominal injuries that prevent the application of local manual compression; systemic or local changes that occur with abdominal volume increase; and fractures or conditions in the lower right limb that contraindicate the performance of passive mobilization of the 1st metatarsophalangeal joint.

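### The entry limits on arterial and intracranial pressure admit some patients whose cerebral perfusion pressure is already at or below the 50 mmHg stopping limit

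*Protocol article*

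**What the plan says.** All references are to the protocol article.

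- **Entry.** The inclusion criteria under Eligibility criteria {10} require "Hemodynamic stability (MAP> 65 mmHg") and "Intracranial Pressure Stability (0 <ICP < 20 mmHg"). The respiratory criterion is "Respiratory stability (PEEP <10cmH_2_O and FiO_2_ < 60"%). Recruitment {15} repeats the two pressure limits as "hemodynamic stability (MAP> 65 mmHg") and "stability of intracranial pressure (0 <ICP < 20 mmHg"). Neither list contains a criterion on CPP, heart rate or oxygen saturation, or an upper limit on MAP.
- **Stopping.** Criteria for discontinuing {11b} states: "The interventions will stop if reached some of the safety values presented below or when the clinical team considers". Intervention description {11a} applies the same rule to both groups. The safety-limits table that follows includes "50 mmHg < Cerebral perfusion pressure". It also bounds MAP (60 to 110 mmHg), ICP (-10 to 30 mmHg), heart rate (40 to 120 bpm) and saturation (above 90%).
- **Order of events.** Under Implementation {16c} the sequence is applied once consent is signed. Under Outcomes {12}, ICP is read 1 h, 30 min and 5 min before the intervention. No section requires the safety limits to be satisfied before the session starts.

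**The concern.** An entry list and a stopping table should fit together, so that anyone who may start is inside every limit at which the session must end. Here the separate margins look comfortable: the MAP floor at entry is 5 mmHg above the stopping floor (65 against 60), and the ICP ceiling at entry is 10 mmHg below the stopping ceiling (20 against 30). CPP, however, depends on both at once, and it has a stopping limit but no entry limit. A patient with low MAP and high ICP can pass both entry limits and still start past the CPP limit.

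For that patient, staff must either stop at once or carry on beyond the limit. In the first case there is little or no five-minute exposure, and the minute-by-minute ICP readings do not describe the technique. In the second the stopping rule is broken. The affected patients also lie at the top of the eligible ICP range, so losing them would be selective with respect to baseline ICP. Sample size {14} gives 25 per group and 50 in total with no stated allowance for losses. Each patient without usable exposure is therefore 1/25 = 4% of an arm.

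**Working it through.** The 50 mmHg limit is a set threshold, not a derived figure, so there is no calculation of the plan's to reproduce. The check is whether the entry region overlaps the stopping region.

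**Inputs**
- MAP > 65 mmHg and 0 < ICP < 20 mmHg (Inclusion criteria; repeated in Recruitment {15}).
- The session stops unless CPP > 50 mmHg (safety-limits table, applied by {11a} and {11b}).
- Assumption: CPP = MAP - ICP. The article gives only the direction of the relation (Background {6a}: lower MAP or higher ICP lowers CPP).

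**Step 1: lower bound of CPP at entry.** 65 - 20 = 45 mmHg. Both entry limits are strict, so 45 is approached but never attained. It lies 50 - 45 = 5 mmHg below the stopping limit.

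**Step 2: lowest eligible value in whole mmHg.** 66 - 19 = 47 mmHg.

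**Step 3: which eligible pairs are at or past the limit.** CPP is 50 or less when ICP is at least MAP - 50. With ICP no higher than 19:

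| MAP | ICP needed for CPP of 50 or less | Eligible ICP values | CPP | Strictly below 50 |
|---|---|---|---|---|
| 66 | 16 or more | 16, 17, 18, 19 | 50, 49, 48, 47 | 3 |
| 67 | 17 or more | 17, 18, 19 | 50, 49, 48 | 2 |
| 68 | 18 or more | 18, 19 | 50, 49 | 1 |
| 69 | 19 or more | 19 | 50 | 0 |
| 70 | 20 or more | none | - | 0 |

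This gives 4 + 3 + 2 + 1 = 10 pairs at or below 50, of which 3 + 2 + 1 = 6 are strictly below. From MAP 70 upward, every eligible ICP gives CPP above 50.

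**Step 4: the limits taken singly.** Entry MAP above 65 lies above the stopping floor of 60. Entry ICP of 0 to 20 lies inside -10 to 30. Neither conflicts alone; the clash comes only from the combination.

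**Step 5: the other stopping variables.** Heart rate, saturation and MAP of 110 or more have stopping limits but no matching entry limit. No two stated figures conflict there. The entry list is simply silent.

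**The case against.** The strongest reply is that the overlap is a small corner and that practice would deal with it. Only MAP of 66-69 combined with ICP of 16-19 is involved, and not every pair within that block. ICP is read three times beforehand, CPP is recorded on a schedule shown in a figure that is not reproduced here, and the clinical team may stop at its own discretion. A patient treated unnoticed beyond a limit is therefore unlikely. All of this stands, and it limits the reach of the point. It does not reconcile the text: no section says that a patient past a limit before the start is not to be randomised.

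It is also fair that CPP = MAP - ICP is not written out. The article takes CPP from the bedside monitor, and different reference levels for the MAP transducer would shift the figures.

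Three stronger readings are tempting, and the article does not support them.
- A reader might infer that eligible patients in general would be stopped at time zero. Only the corner above is affected, and its share is unknown.
- A reader might infer that the safety comparison is corrupted. No listed outcome compares stop rates; the hypothesis concerns ICP, and patients starting past a limit fall to either arm by chance. What can be expected is some truncated ICP series and lost precision.
- A reader might count the absent heart-rate, saturation and upper-MAP entry ranges as further contradictions. They are a related gap. Having no entry criterion on a variable does not conflict with a stopping limit on it.

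That the article condenses a fuller protocol is not an answer on CPP, because both sets of thresholds are printed and clash as printed.

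**Conclusion.** The inconsistency is real but narrow. Assuming CPP = MAP - ICP, the stated entry limits allow CPP to approach 45 mmHg (47 at the lowest in whole mmHg) against a stopping limit of 50. Ten whole-number pairs are at or past the limit, six of them strictly below. The count of pairs is not a proportion of patients, and the article gives no data from which to estimate one. The likely damage is a few randomised patients with truncated or uninformative ICP series, or treated outside the protocol's own limit. It is worth correcting because it concerns safety text, the trial is small, and the correction is cheap. Which threshold should change is a clinical matter on which this review takes no position.

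**What to change.** 1. Reconcile the entry lists in Eligibility criteria {10} and Recruitment {15} with the stopping rules in {11a}, {11b} and the safety-limits table, so that nobody meeting the entry list is already outside a stopping limit. The clinical team decides which values change. The same revision can settle whether heart rate, saturation and upper MAP need a matching statement at entry.
2. State that this is confirmed from the pre-intervention readings already planned, before the allocation is applied. A patient found outside a limit at that point is then not randomised, and the randomised comparison stays intact.
3. In both arms, report any limit already crossed before the start of the intervention separately from stops during the session.

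The cost is protocol wording, notification of the ethics committee and an update of the registry entry, as {25} provides. If the entry side is what changes, a few patients may no longer be eligible. No new measurement is required as long as the planned readings are taken before allocation.

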#### Exclusion criteria

Thoracic fractures: unstable rib, sternal, clavicular, scapular, or vertebralAbdominal injuries that prevent the application of local manual compressionSystemic or local changes that occur with increased abdominal volumeFractures or conditions in the lower right limb that contraindicate passive mobilization of first metatarsophalangeal joint

### Who will take informed consent? {26a}

This study has been approved by the Comité de Ética de la Investigación de Pontevedra-Vigo-Ourense (ethics board of the Galician public health system) with the registration number 2018/446. The informed consent will be given, if they agree, by the next of kin, to whom will be given written information about the participation in the trial. The relatives will be informed that they can withdraw their consent at any time and that they can claim to the Spanish Agency of Data Protection if their rights are not being fulfilled. As severe acute brain injuries have a relatively slow evolution, we do not foresee the patient’s consent.

### Additional consent provisions for collection and use of participant data and biological specimens {26b}

The consent document offers two options: (1) to erase the data after completion of the study or (2) to allow this data to be kept in an anonymized form for future studies.

## Interventions

### Explanation for the choice of comparators {6b}

The used comparator, passive first metatarsophalangeal joint mobilization, allows us to apply a technique that usually patients at this condition receive and that has no known effect in the intracranial pressure.

